### Anesthetic management

All patients will be screened by an anesthesiologist before surgery. On arrival at the operating room, an IV cannula and an invasive arterial cannula will be inserted in the hand or forearm. Fluid administration will consist of a continuous IV infusion of crystalloid solution of 500 cm^3^/h. All patients will receive total intravenous anesthesia with propofol and remifentanil administered using target-controlled infusion (TCI) pumps. Muscle relaxants will only be given prior to intubation to avoid the negative effects of muscle relaxation on the muscle responses. To be able to study the effects of MAP and depth of anesthesia alone, parameters that might influence the mTc-MEP measurements will be kept stable and in between certain ranges:

Propofol will only be administered per TCI pump (i.e. no manual boluses will be administered). The target effect-site concentrations will be selected by the responsible clinician on the basis of the pEEG values as per standard practice in our hospital.Remifentanil will be administered at effect site concentration of 4 ng/ml, using the Minto PKPD model [33, 34].Ketamine use will not be administered during the study.In part 1, vasopressor infusions will be used to maintain the MAP at 70–100 mmHg.In part 2, propofol infusion rates will be adjusted to maintain the pEEG between 40 and 60.The ventilation will be adjusted to maintain normocarbia (end-tidal CO_2_ 4–5.0 kPa; or PaCO_2_ 4.5–5.5 kPa) to avoid the confounding influences of excessive anesthesia and hypocarbia on mTc-MEPs.Core body temperature will be kept close to 37 Celsius, with the use of a routinely used forced air patient warming system.The EV1000 monitor (Edwards Lifesciences, USA) will collect data concerning cardiac output, pulse pressure variation and stroke volume variation. The latter will be kept below 12% during the study procedure.

Data of all abovementioned parameters will be continuously measured and the data will be collected. Other anesthetic considerations specifically for either part 1 or part 2 are explained below at the study procedures.

### Study procedures

This research protocol describes two prospective observational studies that will be performed in two parts. In part 1 we will examine the effects of depth of anesthesia, quantified by pEEG, on mTc-MEP characteristics. In part 2 we will examine the effects of blood pressure, quantified by the MAP, on mTc-MEP characteristics.

Patients that will undergo spinal surgery with the use of mTc-MEPs are eligible for these studies. Patients will either participate in part 1 or part 2. This will not be randomized.

#### Part 1: effect of depth of anesthesia on mTc-MEP characteristics in spinal surgery

After induction of anesthesia and positioning the patient in prone position, and before the onset of the spinal surgery, the effect-site (brain) propofol concentrations will be adjusted to achieve pEEG values according to Fig. 1.

**Fig. 1 Fig1:**
[figure not shown]
Schematic overview study design part 1: effects of depth of anesthesia on mTc-MEP characteristics in spinal surgery. *pEEG* processed electroencephalogram, *Propofol Ce* propofol effect site concentration, mTc-MEP muscle recorded transcranial electrical stimulation motor evoked potential

Although models exist to predict the time course of clinical effects of propofol through its interaction with the GABA_A_ receptor, there remains uncertainty over the accuracy of these models, and of the likelihood of longer-term structural changes following propofol interactions with the receptor. If there are long term effects, then path-dependent differences may exist. Patients will therefore be randomized over two different protocols. One group will start with decreasing propofol concentrations and one group will start with increasing propofol concentrations resulting into the pEEG values as can be observed in Fig. 1. These predefined pEEG values are not in conflict with the current standard care since pEEG ranging from 30 to 60 are common values during spinal surgery. Once a stable pEEG level has been reached, mTc-MEPs will be registered for 5 min and the following will be determined: a voltage threshold to evoke mTc-MEPs and three mTc-MEP measurements, for the left and right TA, GAS and AH muscles. We will perform three mTc-MEP measurements per stable pEEG level to address for the pre-existing variability between mTc-MEPs and average the measurements per stable pEEG level. There will be at least 1 min in between each mTc-MEP measurement to avoid facilitation.

A decrease of the hypnotic component of anesthesia without adequate analgesia (anti-nociception) could lead to increased nociception, increased sympathetic nervous system outflow and blood pressure rise [35]. In this study, however we shall suppress the effects of noxious mTc-MEP stimulation by administering remifentanil at an effect site concentration of 4 ng/ml, using the Minto PKPD model. Based on a previously published study by this research group [36] and the remifentanil package insert, this level of analgesia is enough to ensure adequate anesthesia (combined effect of hypnosis and analgesia) even when hypnotic drug effect is decreased to low hypnotic levels. This will limit the sympathetic outflow and ensure hemodynamic stability.

In order to determine if a combination of pEEG and propofol concentration (estimated effect-site concentration, or measured plasma concentrations) and/or actual MAP during mTc-MEP registrations, better predict mTc-MEP characteristics than the pEEG on its own, in total three blood samples will be taken (10 ml per blood sample) immediately after each of the series of mTc-MEP recordings to measure the propofol plasma concentrations. Propofol Ce values and MAP values will be collected directly after each mTc-MEP measurement as well. See Table 1 for the participant timeline.

**Table 1 Tab1:** Participant timeline

		Before hospital admission	Day 1 of hospital admission	Day 2: procedure Before surgical incision	Day 2: procedure After surgical incision	Day 4/7
1	Approach, information provision	X				
2	Informed consent	X	X			
3	Inclusion in part 1 or 2	X	X			
4	Pre-operative neurological examination		X			
5	mTc-MEP measurements at different pEEG and MAP values			X		
6	Taking blood samples for propofol blood concentrations			X		
7	Collecting propofol Ce, MAP/pEEG values immediately after mTc-MEP measurements			X		
8	Post-operative neurological examination					X

*mTc-MEP* muscle recorded transcranial electrical stimulation motor evoked potential, *pEEG* processed electroencephalogram, *MAP* mean arterial pressure

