#### Part 1: pEEG

##### Primary outcome

For the primary outcome of part 1, a linear mixed effects model will be fitted in which pEEG target (categorical variable with values 30, 40 or 50) will be included as a fixed effect and a random intercept will be used to account for the between-subject variability in the mTc-MEP measurements. Independent normal distributions with mean zero and constant variance will be used to represent the within-subject errors.

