##### Secondary outcome

For the secondary outcome, additional terms for MAP and propofol concentrations (effects site and blood concentration) will be added to the fixed effects structure of the model specified for the primary outcome. The specification of the random effects structure and the residual covariance structure will not change,

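### Part 1 randomises the direction of propofol change because response may be path-dependent, but the stated models contain no direction or order term

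*Protocol article*

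**What the plan says.** Protocol article, Study procedures, Part 1 (text under Fig. 1). The reason for randomising is given as "If there are long term effects, then path-dependent differences may exist", and the consequence as "Patients will therefore be randomized over two different protocols". The two arms are defined by "One group will start with decreasing propofol concentrations and one group will start with increasing propofol concentrations". The allocation ratio is not stated. The remark elsewhere under Study procedures that allocation is not randomised concerns the choice between Part 1 and Part 2, not this step.

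Statistical methods, Part 1, Primary outcome. The fixed part is "pEEG target (categorical variable with values 30, 40 or 50) will be included as a fixed effect". The random part is "a random intercept will be used to account for the between-subject variability in the mTc-MEP measurements". The errors are "Independent normal distributions with mean zero and constant variance will be used to represent the within-subject errors".

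Statistical methods, Part 1, Secondary outcome. Here "additional terms for MAP and propofol concentrations (effects site and blood concentration) will be added to the fixed effects structure", and the random and residual structures stay as they were. The only other analysis named is an optional one for age, under Subgroup analysis.

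The Part 1 sample of 25 is called pragmatic, and the study is described as hypothesis-generating.

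**The concern.** The one factor that Part 1 randomises was introduced for a scientific reason, yet it appears in no objective and no model. This is more than detail left to a later analysis plan: the opening of Statistical methods announces a more precise specification of the models, and the Part 1 text then lists the fixed effects, the random effects and the residual structure. Direction, sequence and period are not among them.

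Two things are at stake. First, the suspected path-dependence cannot be estimated from the planned output, and an analysis of it added later would be post hoc. Second, if response does differ by direction in a level-specific way, that systematic variation is treated as noise and the pEEG contrasts become less precise than the data allow. The reported pEEG effect would then be an unlabelled average over two different curves.

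**Working it through.** **No figure to reproduce.** The 25 patients rest on no alpha, power, effect or SD. The check therefore reads the models term by term and then works out where an omitted direction effect would go.

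**Inputs.** From the protocol: 25 patients, three pEEG targets, recordings averaged per level, two directions. Assumed, because Fig. 1 is not shown and no variances are given: orders 30-40-50 and 50-40-30, a 12/13 split, residual SD σ = 0.30 log units, and a drift of d per step along the sequence.

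**Step 1: what each model can estimate.** The primary model has parameters for three pEEG levels, a patient variance and a residual variance. The secondary model adds MAP and propofol concentrations. None of these is direction, order or direction-by-level. Propofol concentration is no substitute, since path-dependence means a different response at the same level.

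**Step 2: a level-specific or order effect.** Under the assumed orders, drift adds −d, 0, +d across the levels in one arm and the reverse in the other. Patient means do not change, and with near-even groups the level means hardly change. The sum of squares left over is about 25 × 2d² = 50d², on (25 − 1)(3 − 1) = 48 degrees of freedom. The expected residual variance is therefore about σ² + (50/48)d² = σ² + 1.04d². The standard error of the 50-versus-30 contrast is √(2σ²/25) = √(0.18/25) = 0.085 when d = 0, and is multiplied as follows:

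| d per step | √(1 + d²/σ²) | √(1 + 1.04d²/σ²) |
|---|---|---|
| 0.05 | 1.014 | 1.014 |
| 0.10 | 1.054 | 1.056 |
| 0.15 | 1.118 | 1.122 |
| 0.30 | 1.414 | 1.428 |

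Simulation under the same assumptions gave standard errors of 0.095 against 0.084 at d = 0.15, and 0.121 against 0.084 at d = 0.30, without and with an order term. That is 12% and 43%.

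**Step 3: a constant direction shift.** Set both variances to 1 and shift one direction by 1 SD at every level. In simulation the planned model returned a residual variance of 1.00 and a random-intercept variance of 1.26. The within-patient pEEG contrasts are unaffected. Adding direction returned the intercept variance to 1.00.

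**Step 4: bias in the average contrast.** The two arms pull the 50-versus-30 contrast by +2d and −2d, so the net bias is 2d × (difference in group size)/25.
- 13/12 split, d = 0.15: 0.30 × 1/25 = 0.012, or 0.04σ. At d = 0.30 it is 0.024, or 0.08σ.
- 16/9 split, d = 0.15: 0.30 × 7/25 = 0.084, which is 42% of an assumed effect of 0.20.

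**Step 5: which terms are estimable.** Three levels in two directions make six cells. Level, direction and their interaction use six columns of rank 6. Adding a categorical recording period gives eight columns, still of rank 6: under these orders, period is determined by direction and level.

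**Step 6: precision of a direction estimate.** For 12 versus 13 patients at two-sided 5%, 80% power needs a difference at one level of (1.96 + 0.84) × √(1/12 + 1/13) = 2.80 × 0.400 = 1.12 SD. Power is 24% at 0.5 SD, 52% at 0.8 SD and 71% at 1.0 SD. The within-patient interaction does better when drift is large: at d = 0.15 and σ = 0.30, the two-degree-of-freedom test has about 87% power.

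**The case against.** The best defence is that path-dependence is not among the Part 1 objectives or hypotheses. Randomising direction can be read as balancing a nuisance factor, which needs no model term, and the protocol promises no test. With near-even groups the average contrast is then almost unbiased and the standard error errs on the wide side, which is conservative in a study that calls itself hypothesis-generating. Recording only at a stable pEEG level, and adding measured plasma concentrations to the secondary model, also deals in part with simple concentration lag.

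Most of this stands, and it limits the severity. It does not remove the point: balance neither estimates the effect that prompted the randomisation nor takes direction-by-level variation out of the residual. If balance was the only purpose, the text should say so.

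Three stronger readings may tempt a reader and are not supported:
- That the pEEG result is invalid or seriously biased. That would need markedly uneven groups, and the protocol does not describe any.
- That all path-dependence ends up in the residual. A constant shift goes into the random intercept and leaves the pEEG contrasts alone (Step 3).
- That inflation near 40% is to be expected. It needs a drift of one full residual SD per step; at 0.05 to 0.10 per step the loss is 1 to 5%.

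**Conclusion.** The omission is real and does not depend on the missing figure: the stated primary and secondary models leave out the factor that Part 1 randomises, so path-dependence goes unestimated. The cost to the pEEG contrasts lies in precision, ranging from negligible to substantial according to the drift. Bias is small under a near-even split but possible under an uneven one. Every magnitude rests on assumed sequences, SD and drift, and is illustrative only. Severity is moderate: a worthwhile improvement to an exploratory analysis, not a defect that must be repaired before the trial can be interpreted.

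**What to change.** In Statistical methods, Part 1, Primary outcome, add randomised direction and direction-by-pEEG target as fixed effects, and carry both into the secondary model. Report the pEEG contrasts averaged over the two directions. Report the interaction with its confidence interval as an exploratory direction/order effect. State that it cannot separate path-dependence from plain time drift and that power is limited. Do not add a separate recording-period term if each arm visits the three levels once in opposite orders, because it is then aliased with the terms already present; check this against the sequences in Fig. 1.

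The cost is one or two sentences, two of the 48 within-patient degrees of freedom for the interaction, one of the 24 between-patient degrees of freedom for direction, and no new data. If the sponsor does not want this analysis, the minimum is a sentence saying that direction is randomised only for balance and that path-dependence will not be assessed. Stating the allocation ratio would help either way.

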## Background

For complex and high risk spinal surgeries, intraoperative neurophysiological monitoring (IONM) is used, with the aim of detecting and preventing intraoperative neurological injury [1]. For monitoring in spinal surgery, it is advised to monitor both sensory tracts, using somatosensory evoked potentials (SSEPs), and motor tracts, using muscle recorded transcranial electrical stimulation motor evoked potentials, mTc-MEPs [1–4].

The most common warning criterion for possible surgically induced structural neurological injury, is an mTc-MEP amplitude decrease of 50–80% from the baseline value [2, 4–8]. Therefore, an mTc-MEP amplitude decrease of 50–80% warrants immediate exploration of possible causal factors. However, these warning criteria often result in false positive warnings [2]. This can be due to technical issues, but also other factors may influence mTc-MEP amplitudes, including direct effects of anesthetic drugs on neuronal transmission, as well as indirect effects of blood pressure, blood oxygen levels and body temperature resulting in false positive decreases in mTc-MEPs [9–15]. In clinical practice, decreasing the concentration of intravenous anesthetic drugs and elevating blood pressure often help to restore the mTc-MEP amplitude.

It is known that for optimal recording of mTc-MEPs, total intravenous anesthesia (i.e. induction and maintenance of general anesthesia with intravenous infusions of propofol and an opioid) provides more reliable mTc-MEPs than volatile anesthesia (maintenance of anesthesia by administration of a volatile drug through the anesthetic breathing circuit) [16]. However, mTc-MEPs are still very sensitive to the suppressive effects of propofol anesthesia [10, 16–19]. Given the intra- and inter-individual variability in the relationship between blood and effect-site propofol concentrations, and actual clinical effect, it is scientifically important to study the relationship between depth of anesthesia (actual clinical effect) and mTc-MEP characteristics.

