### Sample size calculation

#### Part 1:  pEEG

Very little is known about the quantitative relationship between depth of anesthesia, propofol plasma concentration, and mTc-MEP. There are insufficient data available on which to base a sample size calculation. A pragmatic sample size of 25 patients has therefore been chosen. This study should be regarded as a hypothesis-generating study.

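### Part 1: averaging the three measurements per pEEG level suits the primary contrast, but in the secondary model it discards the within-level pairing with MAP and propofol Ce

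*Protocol article*

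**What the plan says.** All references are to the protocol article.

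- **Study procedures, Part 1 (text under Fig. 1).** At each stable level one voltage threshold is determined and three measurements are made: "We will perform three mTc-MEP measurements per stable pEEG level to address for the pre-existing variability between mTc-MEPs". The same sentence goes on to "average the measurements per stable pEEG level".
- **Study procedures, Part 1 (before Table 1).** "Propofol Ce values and MAP values will be collected directly after each mTc-MEP measurement as well". Plasma propofol is sampled less often: "in total three blood samples will be taken (10 ml per blood sample) immediately after each of the series of mTc-MEP recordings", that is, once per level.
- **Statistical methods, Part 1.** In the primary model "pEEG target (categorical variable with values 30, 40 or 50) will be included as a fixed effect", with a random intercept per patient and independent errors of constant variance. The secondary model adds MAP, Ce and plasma concentration as fixed effects and leaves the random effects and residual structure unchanged. Neither paragraph withdraws the averaging rule, so the models are read here as fitted to level means.
- **Study objectives, Part 1, Secondary objective 1 and its hypotheses.** The question is whether propofol concentration and/or the MAP at the time of registration improves prediction over pEEG alone. The trial expects that pEEG alone does as well as the fuller model.

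**The concern.** MAP and Ce are read nine times per patient to serve secondary objective 1, but the response they belong to is reduced to three values. Within one level the pEEG target is fixed, so any movement of MAP or Ce between the three measurements informs on their effect separately from the pEEG target. A model fitted to level means cannot use that information.

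What is at stake is the precision of the secondary result. The expected finding is that MAP and propofol concentration add nothing. With 25 patients, a wider standard error on the MAP or Ce term makes that finding easier to report when it is not true. In addition, level means alone cannot separate the variance between measurements at constant depth from the patient-by-level variance, because both merge into one residual.

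**Working it through.** **Inputs from the protocol.** 25 patients ("A pragmatic sample size of 25 patients has therefore been chosen"), 3 pEEG levels, 3 measurements per level; MAP and Ce per measurement; plasma propofol and threshold once per level. There is no planned power or variance to reproduce: "There are insufficient data available on which to base a sample size calculation".

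**Assumed inputs.** q = patient-by-level variance divided by measurement variance, 0 to 2. r = within-level SD of MAP divided by its between-level SD, 0.1 to 1. The six muscles are not modelled jointly.

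**Step 1: rows.** Separate measurements give 25 × 3 × 3 = 225 rows per muscle; level means give 25 × 3 = 75.

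**Step 2: primary contrast.** The pEEG target is constant within a level, so in balanced data the estimate is a difference of level means either way. In one simulated balanced data set both fits gave 0.181 and 0.446 for the two contrasts. The error term does differ:

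- Level means: t = contrast / √(2·MS_level/75), 48 df.
- Single measurements with the patient intercept only: the same contrast over √(2·MS_pooled/75), where MS_pooled = (SS_level + SS_within)/198.

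In units of the measurement variance, MS_level has expectation 1 + 3q and MS_pooled has (48(1 + 3q) + 150)/198. At q = 0.25 these are 1.75 and (84 + 150)/198 = 1.18, so the pooled version is too small. In 20,000 simulations per setting, the two-sided 5% test on single measurements rejected a true null in 7.5% (q = 0.1), 10.8% (0.25), 14.8% (0.5), 19.8% (1) and 24.9% (2) of cases. Level means stayed at 4.8–5.1%. Under the stated model, averaging therefore protects the primary test.

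**Step 3: MAP slope in the secondary model.** Set the measurement variance and the between-level variance of MAP to 1.

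- Information kept by level means: 48 × (1 + r²/3)/(q + 1/3).
- Information within levels, discarded by averaging: 150 × r², where 150 = 25 × 3 × 2.
- Share lost = within/(within + kept). Averaging multiplies the standard error by 1/√(1 − share).

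Example, r = 0.25 and q = 1: kept = 48 × 1.0208/1.3333 = 36.75; within = 150 × 0.0625 = 9.375; share = 9.375/46.125 = 20.3%.

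| r | Lost, q = 0 | Lost, q = 0.25 | Lost, q = 1 | SE multiplied by |
|---|---|---|---|---|
| 0.1 | 1.0% | 1.8% | 4.0% | 1.005–1.021 |
| 0.25 | 6.0% | 10.0% | 20.3% | 1.031–1.120 |
| 0.5 | 19.4% | 29.6% | 49.0% | 1.114–1.401 |
| 1 | 43.9% | 57.8% | 75.8% | 1.335–2.031 |

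The same formula applies to Ce with its own r. It does not apply to plasma propofol or the threshold voltage, which have no replicates within a level.

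**The case against.** The case for leaving the plan alone has several parts.

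- *Averaging is reasoned and suits the primary model.* This stands in full; Step 2 supports it.
- *MAP will hardly move within a level.* Registration lasts 5 minutes at stable pEEG, and the protocol expects remifentanil to keep haemodynamics stable. The 70–100 mmHg band under Anesthetic management is the range maintained in part 1, not the expected drift within one registration. This stands as a limit on size: the r = 1 row needs MAP to vary as much within a level as between levels, and the documents give no ground for that. A reader might infer that the standard error could be halved, but the documents do not support it.
- *Nothing is lost for good.* Data management exports the IONM recordings before amplitude and AUC are calculated, and nothing says that single measurements are thrown away. Part 1 is also declared hypothesis-generating. So the loss lies in the planned analysis, not in the data.
- *Variability between measurements is not a study question.* A reader might infer that it drives false warnings, since the Background says that "an mTc-MEP amplitude decrease of 50–80% warrants immediate exploration of possible causal factors". But the Background attributes false positives to technical issues, anesthetic drugs, blood pressure, oxygen and temperature, and no objective concerns this variability or the rate of crossing 50% or 80%. That stronger reading is not supported.

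What remains is narrow: the protocol collects MAP and Ce per measurement for a declared objective, and its averaging rule prevents the model for that objective from using the pairing.

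**Conclusion.** The point holds for the part 1 secondary model of amplitude and AUC with MAP and Ce, and only there. The primary pEEG contrast loses nothing.

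The loss of information on the MAP slope is about 1–4% at r = 0.1, 6–20% at 0.25 and 19–49% at 0.5, for q from 0 to 1. It is negligible if MAP is steady within levels and worth recovering if it is not; the documents do not show which applies. The figures also rest on balanced data, independent errors between measurements within a level, one added covariate at a time, and a slope that is the same within and between levels.

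**What to change.** - Keep level means for the primary outcome and for the threshold voltage.
- For the secondary model of amplitude and AUC, enter the three measurements per level as separate rows, each with its own MAP and Ce. Use random intercepts for patient and for pEEG level within patient. The second intercept is essential: without it the replicates count as independent and the error inflation of Step 2 appears.
- Keep plasma propofol as a covariate with one value per level.
- Report the within-level variance from this fit.
- The proportions of falls reaching 50% or 80%, between and within levels, are an optional extra. If reported, define the pairing first: two levels with three measurements each give 3 × 3 = 9 possible pairs per patient.

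Cost: a change of wording in Statistical methods and one more variance component to estimate. No new measurement is needed, and in balanced data the pEEG contrast without covariates does not change.
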